#### Eligibility criteria

##### Inclusion criteria

Women who were enrolled in the WF trial and also allowed to collect their biological samples at 12 and 32 weeks of gestational age will be included in this study.Husbands of the above-identified women will be included.

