### Study purpose

The purpose of this study is to explore factors associated with anemia among women of the reproductive age group in Thatta district using mixed methods approach.

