Likewise, other observational and interventional studies, MNHR provided a platform and existing research infrastructure to conduct an individually randomized controlled trial known as Woman First Trial (Preconception maternal nutrition). This trial aimed to determine the benefits to the offspring of women in poor, food-insecure environments of commencing a daily comprehensive maternal nutrition supplement ≥ 3 months prior to conception versus the benefits of commencing the same supplement at 12–14 weeks of gestation and also to compare offspring outcomes with those of a third trial arm who received no supplementation [21]. Study’s intervention included daily 20 g lipid-based (118 kcal) multi-micronutrient (MMN) supplement and, for women who were underweight or had slow gestational weight gain, an additional protein energy supplement was provided. The primary hypothesis of the study was that in women living in poor, food insecure populations, commencing a maternal nutrition supplement at least 3 months prior to pregnancy (Arm 1) would result in significantly greater fetal linear growth than starting the same nutrition supplement at 12–14 weeks gestation (Arm 2) or than not providing this supplement (Arm 3) [21]. The details of the Women First trial including design, study sites, follow-ups, various stages and ethical approvals are discussed in depth elsewhere [21].

For the current study regarding factors and perception of anemia, we propose to recruit conveniently mother-father pairs from 9 Union councils (UCs) of the district Thatta, where MNHR is currently based and subjects previously gave biological samples in Woman First (WF) trial. In addition, we will also enroll health care providers such as female and male doctors providing health services to the people of Thatta, traditional birth attendants (TBAs) who are one of the important stakeholders providing care to the women and lady health visitors or midwives who are also engaged in providing health care services to women Table 1.

**Table 1 Tab1:** Number of Participants for Qualitative phase

Number of participants for the qualitative phase	Sample Range
Participants for Key-informant Interviews (KIIs)	
Healthcare providers at District Thatta (Doctors/LHVs/TBAs/Managers)	10 KIIs
Participants for Focus Group Discussion (FGDs)	
The mother who were enrolled in WF trial	5 FGDs (6–8 participants in each group)

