#### Sample size and sampling method

A minimum sample of 150 women will be required in order to achieve a power of 80% at 5% level of significance, keeping proportion of anemia among women of reproductive age group from 21 to 75%, anticipated proportion of various risk factors in the range of 20 to 75% among anemic group and 20 to 82% among non-anemic group. In addition to 150 women, their spouses will also be included thus making a total of 300 participants to achieve the objective of quantitating phase of the proposed study. A probability simple random sampling technique will be used to select the participants. A sampling frame will be generated from existing data of WF participants and participants will be identified randomly from the given list by a third person mainly the data manager of MNHR.

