#### Data analysis

Quantitative data will be double-entered in EPI-Data software. The primary outcome of analysis will be anemia which has been defined in agreement with WHO definitions for anemia, which are Hb < 12.0 g/dl or Hct < 36% for non-pregnant women [22]. Frequencies and percentages will be calculated for qualitative variables like working status, education level, and employment status, the occupation of the woman and her husband, any pre-existing medical conditions. Means and standard deviations or median with inter-quartile range whatever will be appropriate for the continuous variables including current age of the woman, age at the time of marriage, parity, number of alive children and number of prior sons etc. will be generated for all participants.

Univariate analysis will be conducted by computing unadjusted odds ratio (OR) and their 95% confidence intervals to compare the anemic and non-anemic women with respect to all the possible biological and socio-demographic factors. The appropriate test for example chi-square will be used to assess the association between variables. Multicollinearity between independent variables will be assessed. The variables for which *p*-value turns out to be less than 0.25 will be included in the multivariable analysis. In the multivariable analysis, multiple logistic regressions will be used to compute the adjusted odds ratio with 95% confidence intervals. During this analysis interaction between the variables will be assessed. This analysis will also be helpful in identifying the potential confounders related to the study. Data will be analyzed using SPSS version 19.0 version.

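### Phase 2 samples only former Women First participants and leaves trial arm out of its models, yet speaks for women of reproductive age across Thatta

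*Protocol article*

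**What the plan says.** Sample size and sampling method (Phase 2): "A sampling frame will be generated from existing data of WF participants", from which 150 women are drawn at random, with their husbands. The Phase 2 inclusion criterion admits "Women who were enrolled in the WF trial and also allowed to collect their biological samples at 12 and 32 weeks of gestational age". Currently pregnant women are excluded.

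Study setting and participants: recruitment takes place in 9 union councils, and the district has 30. The same section describes WF as an individually randomised trial in poor, food-insecure settings. Its "intervention included daily 20 g lipid-based (118 kcal) multi-micronutrient (MMN) supplement" started at least 3 months before conception in one arm and at 12–14 weeks in another. The trial was "also to compare offspring outcomes with those of a third trial arm who received no supplementation". Underweight women and those with slow gestational weight gain received an additional protein-energy supplement.

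Data analysis (quantitative): unadjusted odds ratios will "compare the anemic and non-anemic women with respect to all the possible biological and socio-demographic factors". Variables with p < 0.25 go into a multiple logistic regression, which gives the adjusted odds ratios. The laboratory factors listed under data and sample collection include iron, ferritin, B12 and folic acid. WF arm is named neither in data collection nor in the analysis.

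Study purpose: to "explore factors associated with anemia among women of the reproductive age group in Thatta district". The objectives use the same target. The Discussion expects to identify types of anemia for policy in rural Pakistan and to inform the health of reproductive-age women throughout the district.

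**The concern.** There are two linked problems.

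The first is the population. A random draw from the WF list represents that list. Women never enrolled in WF, those who did not conceive in it or lost the pregnancy before 32 weeks, and those who declined sampling cannot enter. No passage limits the inference to the women who can. The mix of anemia types, which the Discussion wants to use for policy, depends directly on who is sampled.

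The second is the supplement. Several of the main biological factors are nutrient levels, and part of the frame was randomised to a product meant to improve nutrition. If the supplement still influences both a nutrient marker and hemoglobin by a route other than that marker, arm is a common cause of the two. Some of the association between marker and anemia would then be left over from the old randomisation. The plan records each woman's WF ID, so arm can be linked, but nothing says that it will be.

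**Working it through.** **1. Population, side by side.**
- Target (purpose, objectives, Discussion): women of reproductive age in Thatta.
- Frame (sampling method, inclusion criterion): WF enrolment, and samples at 12 and 32 weeks, hence a pregnancy that reached 32 weeks.
- Area: 9/30 = 30% of union councils.

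The frame is a narrow subset of the target. This part needs no assumption about the supplement.

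**2. The plan's figure.** I take 150 women as given. The power statement offers only ranges, so no single sample size can be reproduced from it. The point does not depend on that.

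**3. Where arm can confound.** Randomisation makes arm independent of factors fixed beforehand, apart from chance and any selection introduced by the 32-week condition. The concern is therefore limited to factors the supplement could alter: iron, ferritin, B12, folate and anthropometry, together with the frequency and mix of anemia.

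**4. Crude odds ratio for a null factor (illustration).** Assumptions not in the documents: equal thirds, so 2/3 supplemented; persistent effects; no association between low B12 and anemia within either group. Each cell is 1/3 × (unsupplemented product) + 2/3 × (supplemented product).

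| | Low B12, unsuppl. / suppl. | Anemia, unsuppl. / suppl. | Crude OR |
|---|---|---|---|
| (a) | 50% / 33% | 65% / 53% | 1.08 |
| (b) | 50% / 23% | 70% / 48% | 1.28 |

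For (b):
- low B12 and anemic: 1/3 × 0.50 × 0.70 + 2/3 × 0.23 × 0.48 = 0.1903
- the other three cells by the same rule: low B12 and not anemic 0.1297; normal B12 and anemic 0.3631; neither 0.3169
- OR = (0.1903 × 0.3169)/(0.1297 × 0.3631) = 1.28

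With 150 women these cells hold 28.5, 19.5, 54.5 and 47.5. So SE(log OR) = √(1/28.5 + 1/19.5 + 1/54.5 + 1/47.5) ≈ 0.355, and the 95% interval spans a factor of exp(1.96 × 0.355) ≈ 2.0 either way.

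**5. Frequency of anemia (illustration).** Let p0 be the unsupplemented prevalence and OR the assumed supplement effect on current anemia. Then ps = OR·o/(1 + OR·o) with o = p0/(1 − p0), and the shift is 2/3 × (ps − p0).
- p0 = 50%: −11.1 points at OR 0.5; −1.8 at OR 0.9.
- p0 = 75%: −10.0 points at OR 0.5; −1.4 at OR 0.9.

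The 95% half-width, 1.96·√(p(1 − p)/150), is 8.0 points at 50% and 6.9 at 75%.

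**6. Would the screen keep arm?** Suppose a supplemented-or-not term were offered to the p < 0.25 screen, with 100 women against 50. The chance of passing is Φ((d − 1.150·SE0)/SE1) plus the small opposite tail. SE0 is the pooled and SE1 the unpooled standard error.
- p0 = 50%, OR 0.7: ps = 41.2%, d = 0.0882, SE0 = 0.0860, SE1 = 0.0862. The chance is 0.451 + 0.015 = 0.47, so arm is dropped 53% of the time.
- p0 = 75%, OR 0.7: dropped about 58%.
- OR 0.5: dropped about 21% (p0 = 50%) or 24% (p0 = 75%).

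At the 5% level, power for the arm effect would be 44–51% at OR 0.5 and 14–18% at OR 0.7. A non-significant arm term would not be reassuring.

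**The case against.** **The list of factors is open, and an unseen analysis plan may include arm.** The section does promise to consider all possible factors and to look for confounders. But it names two kinds, biological and socio-demographic, and randomised arm is neither. It also fixes the entry rule, and step 6 shows that this rule could remove arm even if it were offered.

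**Arm was randomised, so it cannot confound.** This stands for factors fixed before randomisation, which covers hemoglobinopathy and much of the socio-demographic objective. A reader might infer that every biological association is confounded; the documents do not support that.

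**The planned result is an adjusted odds ratio.** This also stands. If iron, B12 and folate enter together, part of the supplement's path to hemoglobin is blocked. The crude figures in step 4 are not a forecast of bias in the final model, and even the upper one is small beside an interval spanning a factor of 2.

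**The frame is disclosed, and the conclusions are hedged.** The article openly says that participants come from WF, calls the work a sub-study, and plans no formal district prevalence estimate. That lessens the fault, but the objectives still state the wider target without qualification.

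**Two further inferences go too far.** A reader might conclude that never-married women are barred. No criterion says so, and marital status is collected. A reader might also call it an error that the quantitative analysis names no use for the 12- and 32-week samples. A sub-study may define its frame by earlier sampling, and whether to use those samples is a design preference.

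**Conclusion.** The concern holds in a limited form. The mismatch between frame and stated population is plain from the text and would remain even if the supplement had no lasting effect. The omission of arm is a real gap for nutrient markers, anthropometry, and the frequency and type of anemia.

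Its size cannot be determined. The documents give no allocation ratio, no time since supplementation, no effect on current hemoglobin and no list of the supplement's micronutrients. The crude odds ratios of 1.08 to 1.28 and the prevalence shifts of 1.4 to 11.1 points are illustrations under assumed effects. They shrink towards nothing if the effect has faded. It would be tempting to say that the results will describe a largely supplemented cohort, but that rests on assumed equal allocation.

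**What to change.** 1. Restate the target in the purpose, objectives and conclusions as non-pregnant women previously in the WF trial who carried a pregnancy to at least 32 weeks, in the 9 union councils. Limit anemia-type results to that group.
2. Merge WF arm from the trial database by WF ID.
3. Keep arm, whatever its p-value, in the adjusted models for nutritional and anthropometric factors. It is not needed to remove confounding of factors fixed before randomisation.
4. Report anemia and anemia type by arm. This gives some view of whether an effect persists, subject to the limited power in step 6.

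The cost is a database merge, a narrower conclusion, and two degrees of freedom for three arms or one for supplemented-or-not. That matters at the extremes of the plan's prevalence range. At 21% anemia there would be 150 × 0.21 = 31.5 anemic women, and at 75% there would be 150 × 0.25 = 37.5 non-anemic women. If the smaller group is of that order, use the single term. No new visits, samples or participants are needed.

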##### Exclusion criteria

Women who are pregnant at the time of data collection.Women and their husbands who do not agree to participate in this study will be excluded.

### Data collection method

We are proposing to recruit from mother-father pairs of subjects previously enrolled and gave biological samples in WF. New samples to be collected in the proposed sub-study include blood samples and stool samples only from women of previously enrolled WF participants. Around 12–15 mL of venous blood will be collected by the trained and professional phlebotomist. Blood samples will be used to do the investigations such as complete blood count (CBC), the presence of the malarial parasite, Iron levels, Erythrocyte Sedimentation Rate (ESR), C-Reactive Protein Test (CRP), B-12 and folic acid levels and identification of hemoglobinopathies through hemoglobin (Hb) electrophoresis. In addition, the hemoglobin of enrolled women will also be checked by using the hemocue machine to be consistent with WF primary study methods and to see the differences between hemoglobin levels being measured by taking venous blood and by making finger prick. Likewise, stool samples will be used to assess the worm infestation. In this study, no biological sample will be collected from husbands of the participating women; except the hemoglobin levels which will be checked by using hemocue machines and a small questionnaire will be administered to husbands to collect the data on their socio-demographic factors.

### The detailed procedure for data collection

The home visitor research assistant (HVRA) responsible for collecting the data for WF primary trail will be trained in the proposed study to administer new questionnaires while visiting their households. In the field, HVRA will discuss the purpose of the study with the whole family and will also assess the eligibility of woman before taking consent from her. In order to check the pregnancy status, HVRA will take a brief history of last menstrual period and symptoms of pregnancy in the local language. In addition, she will also perform a pregnancy urine test to confirm the pregnancy status of the woman. A woman will be excluded from the study if a positive pregnancy test is found and will be included in the study otherwise. After woman understands the procedures of study completely, HVRA will take a written informed consent from a woman. Once informed consent is obtained, the HVRAs will 1) administer the relevant questionnaires, 2) conduct anthropometric measurements (weight, height, body mass index, waist circumference, hip circumference, mid-upper arm circumference, and head circumference.) and 3) will also facilitate phlebotomist to collect the biological samples at different collection points of AKU. At the end of the questionnaire, a section will be provided for the data collectors to note down any important information they got during the interview. The questionnaire will have the interviewer’s name mentioned on it as well as the date of the filling of the form and information about the contact number of the investigator and the contact number and/or the address of the respondent, so that any queries at the field or anywhere in between the study can be addressed in an efficient manner.

In addition, male community mobilizers will contact the husbands of the eligible women in order to enroll them in the study. Likewise, male community mobilizers will approach to husbands of identified women and will ask some information related to their socio-demographic factors, personal habits, and daily routines by administering a structured and pre-tested questionnaire. Like HVRAs, male community mobilizers will exactly follow the same procedure of taking written informed consent from husbands.

Our trained HVRAs and male community mobilizers are native speakers of the local languages and are familiar with the culture will carry out consenting and procedures in the local language. For those participants who are illiterate, a family member of their choice or a member of the community who is not part of the research staff will serve as a witness. The HVRAs and male community mobilizers will explain the study and allow the family to ask any questions about it and to discuss it among themselves. Comprehension will be attested by asking the participant to describe the study in their own words. If the family would like to continue with the data/sample collection, they will be asked for written informed consent in the local language.

### Biological sample collection, transportation, and analysis

Two types of biological samples (blood and stool samples) will be collected from enrolled women in the proposed study. There are three different blood collection points in the catchment area of MNHR in district Thatta where samples will be collected. HVRAs will inform women at least 1 day before to collect biological samples from them and they will fix an appointment with them as per their availability and convenience. After informing women, HVRAs will visit women at their homes and will bring them to the blood collection points of AKU. Each sample collection is completely voluntary and can be denied at any time. Written informed consent will be obtained separately before any sample collection occurs.

At the blood collection point, a trained and qualified phlebotomist will greet the woman and explain the procedures of blood collection to her. The phlebotomist will collect blood samples from the woman by following universal precautions and standard procedures of AKU laboratory. A unique number and barcode will be assigned to each sample being collected from the woman and relevant information such as name and unique WF ID of woman and names of investigations (CBC, iron, B12 etc.) will be entered into the computer on the spot. The woman can submit the stool sample on the same day or she will be guided by HVRA to give stool sample the next day. A complete kit including clean sheet, gloves, Coleman box with ice packs and stool container with scoop will be provided to every woman to pass and store stool sample in a clean area on appropriate temperature. HVRA will contact the woman on the next day to inquire if she has passed stool sample and will collect the sample from woman to submit the same on appropriate collection point. This whole procedure of data collection along with biological sample collection will take about 60–90 min to complete the data collection from each individual participant.

All biological sample being collected from enrolled women will be transferred from Thatta collection points to the main Aga Khan Hospital Karachi Pakistan under the required cold chain. The main laboratory of the Aga Khan University Hospital Karachi is well equipped and has the capacity to analyze the blood samples for the proposed markers and investigations such as complete blood count (CBC), serum iron, folic acid, Erythrocyte Sedimentation Rate (ESR), C-Reactive Protein Test (CRP), B12, ferritin, hemoglobinopathies, the presence of malarial parasite and stool analysis for worm infestation. Biological samples will be stored and analyzed in the Aga Khan Hospital laboratory by qualified personnel. The remaining samples will be destroyed as per AKU laboratory policy at the end of the study mainly after the analysis is done and reports are generated. Once the laboratory reports are generated, HVRAs will hand over reports to the women and will advise and facilitate them to contact local health care provider for getting health services free of cost from district hospital if required.

### Data management and quality assurance

#### Data monitoring and quality assurance

Regular supervision of the HVRAs in the respective geographic areas will be conducted by the field supervisors who are experienced and have been working in the catchment areas for the last ten years. Each field supervisor will be assigned five geographic areas to make supervisory and monitoring visits and to provide on jo coaching to HVRAs. These field supervisors will review the filled questionnaire to ensure that all sections of the questionnaire are filled properly and consistency checks with skip patterns have been followed correctly before leaving the home of the participant. In addition, Principal investigator (PI) and research coordinator (RC) of the study will also review forms and make surprise visits to monitor the data collection and to guide HVRAs and field supervisors whenever necessary. These filed supervisors will also update PI about the daily progress of the study via phone calls and by sending a summary report on the WhatsApp group generated for this study.

Quality of data collection will be ensured by proper training of the HVRAs and field supervisors. Quality will also be ensured through supervision and random inspection of the data collection process by the principal investigator or senior research coordinator in the field. In addition, meetings will be arranged to maintain coordination among the members of the team and to keep the members up-to-date and to resolve any field related issues.

